## Abstract

**Background:**

Adolescents in residential substance use disorder (SUD) treatment have poor outcomes post-discharge, with follow-up studies suggesting that most adolescents relapse within 90 days. Parenting practices directly influence adolescent SUD outcomes, but parents of adolescents with SUDs are difficult to engage in traditional behavioral treatments. The current study adapts and evaluates a technology-assisted intervention for parents of adolescents in residential SUD treatment. Based on pilot qualitative data with parents, adolescents, and residential staff, we augment an existing computerized intervention (Parenting Wisely; PW) with four in-person coaching sessions, personalized text messages, and an expert-moderated online parent message board. We hypothesize that parents will find enhanced PW (PW+) both feasible and acceptable, and that adolescents whose parents receive PW+ will have better post-discharge outcomes than adolescents who receive standard care (SC) only.

**Methods/design:**

A two phase approach is used to adapt and evaluate PW+. Phase 1 consists of an open trial with 10 parents of adolescents (age 12–17) in residential SUD treatment. Post-discharge qualitative and quantitative data from parents and adolescents will support PW+ refinement. Phase 2 is a randomized pilot trial with 60 parents testing the effectiveness of adding PW+ to SC. Adolescents and parents will complete assessments at baseline, 6-, 12-, and 24-weeks post-discharge. Primary outcomes will be measures of feasibility and acceptability. Secondary outcomes will include adolescent substance use, truancy, high-risk sexual behavior, and criminal involvement. Two parenting processes (monitoring and communication) are examined as potential mediators of change.

**Discussion:**

This study will adapt and evaluate a technology-assisted parenting intervention as a means of improving adolescent outcomes following residential SUD treatment. Results have the potential to advance the field by: addressing a high-risk population, improving parental engagement; targeting parenting practices (putative mediators of change) that have been linked to adolescent outcomes; and developing a highly disseminable approach.

## Background

According to the most recent data from the National Survey of Substance Abuse Treatment Services, there are 3450 residential substance use treatment facilities in the United States and 10.3% of all adolescents who seek treatment for a substance use disorder (SUD) will receive treatment in this setting [1]. Adolescents with SUDs who require a residential level of care typically have the most severe symptoms and the highest rates of psychological, behavioral, legal, motivational, environmental, and vocational problems [2, 3]. Adolescents in residential SUD treatment are also at extremely high risk of relapse, with follow-up studies suggesting that 60% of adolescents discharged from residential SUD facilities will relapse within 90 days [4–6]. Despite such high relapse rates, the majority of adolescents in residential treatment either do not link to or only participate minimally in continuing care after discharge [7, 8]. In recognition of these challenges, a review of the continuing care literature [9] advised treatment developers to supplement or replace traditional clinic-based approaches with new service delivery approaches that are of lower burden and greater convenience, and that facilitate sustained contact with the patient for an extended period of time. Consistent with these recommendations, this study aims to adapt and evaluate a flexible, low cost, low intensity treatment model for parents preparing for their teen’s discharge from residential treatment.

### Rationale for targeting parents

Parents have been established as a critical influence on adolescents’ initiation and maintenance of substance use [10], as well as their substance use outcomes and likelihood of relapse following treatment [11]. Two parenting processes that appear to be particularly important protective factors against adolescent SUDs are monitoring and supervision [12] and communication with the adolescent [13]. Parental monitoring has been identified as a pivotal factor in the initiation of adolescent substance use [10, 14–17] and several studies have implicated parental monitoring as a mechanism underlying adolescent substance use. For instance, one study of 4731 adolescents found that perceived parental monitoring had unique mediating effects on adolescent substance use [18], while other studies concluded that lax parental monitoring was one of the pathways through which parental substance use influenced adolescent substance use [19, 20]. Parental communication also appears to have important protective influences for adolescents with SUDs [10, 21, 22], with studies suggesting that the content, context, style and timing of communication about substance use are all important deterrents of use [23]. Several studies suggest that parenting interventions should target parent-teen communication about the parents’ attitudes toward substance use [24, 25]. One study [26] found that communicating strong parental norms against teen substance use reduced the risk of initiation in early adolescence, while two studies found that communicating disapproval of substance use predicted less alcohol use later in adolescence [24, 27].

Systematic reviews and meta-analyses of treatment approaches for adolescents with SUDs [28–31], including one conducted by this protocol’s Principal Investigator (PI; protocol first author) [32], have found that intervention models that include parents outperform other approaches and are supported by high quality evidence. In Kumpfer et al.’s [33] review of interventions for adolescents with SUDs, family-based interventions that involved a parent or caregiver had average effect sizes 2–9 times larger than adolescent-only interventions. A more recent meta-analysis by Tanner-Smith and colleagues [31] similarly found that family-based interventions outperformed other evidence-based behavioral treatment approaches. Numerous other studies have provided evidence that parent involvement in treatment can improve adolescent engagement, retention, and substance use outcomes [34–36]. This body of research provides justification for: (1) working with the parents of adolescents in residential treatment for SUDs and (2) for targeting parenting skills as a potential mechanism of change in adolescent SUD treatment outcome.

### Limitations of prior parenting interventions

A key limitation of existing interventions for parents of adolescents with SUDs is the difficulty ensuring that parents receive an adequate “dose” of the intervention. In a 2014 systematic review of adolescent SUD interventions [28], those family models identified as “well-established” or “probably efficacious” ranged in intensity from 12 to 24 in-person sessions. Such a high dose of in-person sessions may be especially challenging for parents of adolescents transitioning out of residential SUD treatment, who are often difficult to engage in follow-up care [5]. Studies of adolescents discharged from residential SUD treatment demonstrate that only 36% will attend any continuing care sessions in the community [37]. Moreover, data from community treatment samples indicate that most adolescents who do attend treatment will drop out prematurely [38]. The few studies that have reported high retention rates of parents (i.e., [5, 8]; average of 14.4 sessions of continuing care) have predominantly relied upon home-based sessions or visits, an approach that may be challenging to implement within community programs that often lack adequate staffing and financial resources [39]. To date, there are no treatment models designed specifically to enhance parental engagement or increase parenting skills following the adolescent’s discharge from residential treatment. Thus, the current protocol addresses gaps in extant treatment options by adapting a low-cost, low intensity treatment model that addresses parent engagement and targets key parenting processes (i.e., monitoring and communication) within the prototypic constraints of an acute community residential program.

### Rationale for technology-assisted interventions

To improve upon currently available parenting interventions, it is critically important that any new approach is not only effective, but also acceptable and feasible for both residential treatment center staff and parents. Technology-assisted interventions can potentially better fit the needs of both clinical staff and parents in a number of ways [40, 41]. First, technology-assisted programs have the key advantage of balancing flexibility with fidelity, by allowing the content to be individually tailored to the patient’s specific needs, while retaining core content elements. Second, technology-assisted interventions can be delivered at low-cost with low burden on staff time, thereby ameliorating well-documented challenges to implementing evidence-based interventions such as limited financial resources, front line staff availability, and supervisory support [42, 43]. Third, online programs delivered via computer or smartphone are especially promising due to ease of access. Eighty-seven percent of American adults report using the internet, including 77% of adults in households that earn below $30,000 [44]. Rates of internet usage among adults age 30–49 (a common age range of parents of adolescents) are even higher at 91% [44]. Fourth, recent studies have provided promising support for the effectiveness of computerized or online treatments for adolescents with substance-related problems as additives or alternatives to clinic-based therapy [45–49]. However, these studies have primarily focused on cigarette use [50], prevention rather than intervention [51, 52], and on the adolescent only without involving parents [53].

One online parenting intervention that has promise for parents of adolescents in residential SUD treatment is Parenting Wisely (PW [54]). PW is an internet-based, self-paced program that consists of nine modules. Each module addresses how to handle a common parenting problem including: addressing adolescent substance misuse, monitoring friends, and improving parent–child communication. Five prior studies (two open trials [53, 55], one control-matched trial [56], and two small randomized controlled trials [57, 58]) have specifically tested PW as an intervention for parents of children with behavior problems. Findings across these studies indicated that parental receipt of PW is associated with improvements in parental knowledge and social problem solving skills and reductions in child problem behaviors (measured by the Eyberg Child Behavior Inventory [59]), with medium to large effect sizes.

A recent NIDA funded pilot study (R44 DA026658) was the first to evaluate PW as an adjunct intervention among parents of adolescents with SUDs, all of whom were court referred due to marijuana use. The study compared an educational substance use intervention to a motivational enhancement therapy (MET) with PW. Unpublished pilot analyses of the 3-month outcomes ([name], private communication) based on 128 cases demonstrated that MET + PW had statistically significant beneficial effects relative to education on parent reports of adolescent emotional problems, conduct problems and total behavior problems. In addition, MET + PW produced reductions in adolescent alcohol and drug use relative to education, but the difference was not statistically significant. Further analyses indicated a significant dosage effect for PW: completion of more PW modules was associated with significantly greater reductions in adolescent alcohol and drug use. Effect sizes were generally small in magnitude. This body of work provides evidence in support of PW as a means of reducing child behavior problems [36–38], with some pilot data suggesting that PW has the potential to address adolescent SUDs.

Although the data in support of PW are promising, use of the program is limited when delivered online only. For instance, a 2013 study [60] compared four different PW delivery models and found that delivery of PW content via 5 weeks of in-person groups resulted in significantly larger improvements in parenting skills than PW delivery via internet only. This is consistent with data indicating that new technology-delivered applications are often limited by lack of sustained use; for instance, in 2015, 25% of phone apps that were downloaded were only used once in the first 6 months of ownership [61]. The true challenge therefore is not developing new and exciting technology-delivered interventions, but the “need for collaborative techniques to enhance and maintain usage in vivo to improve therapy outcomes” [62]. A number of studies of adults and adolescents have shown that technology-delivered interventions have positive, sustained effects when combined with low intensity in-person support [63–65]. Thus, instead of comparing in-person versus online delivery, this protocol tests the potential value of an *additive* (in person + online) technology-assisted approach. Furthermore, this protocol augments the PW program with other technology-assisted parental engagement strategies.

### Overview of adaptations to Parenting Wisely tested in this protocol

This protocol examines three adaptations to the PW online model based on qualitative pilot data from 13 parents (7 parents of females, 6 parents of males), 11 adolescents (5 females, 6 males) in residential treatment, and three residential treatment staff (see Table 1 for summary of themes) that were collected as part of a larger qualitative study [66, 67]. First, based on qualitative data indicating that parents did not want to lose the “human element” of treatment, we offer parents up to four in-person coaching sessions. The first two sessions are offered while the adolescent is receiving residential treatment, the time parents described as easiest to attend sessions, in order to capitalize upon parental involvement with the residential treatment program. Second, in response to feedback that parents wanted convenient access to an expert and to other parents post-discharge, parents will receive access to an expert-facilitated online message board. Finally, in order to reinforce usage of PW and the online parent board, parents will receive two text messages weekly containing links to videos of parenting skills, messages of encouragement, and links to the online message board. Such supports are designed to sustain parental engagement, reinforce important parenting skills, and provide easier access to a treatment provider during a time when adolescents are at high risk of negative outcomes, but parents reported it was especially difficult to attend in-person sessions.

**Table 1 Tab1:** Qualitative themes about parenting interventions revealed in pilot data collection with 13 parents, 11 adolescents, and 3 residential staff

Theme	Group	Findings
Parent only sessions	Parent	Parents wanted more (and not fewer) “parent only” sessions
		Parents wanted “parent only” sessions incorporated into existing visits/obligations when possible
	Staff	Residential staff described typical “parent only” sessions as focused on case management
Parenting skills	Parent	Parents were interested in learning new ways to manage their teen’s behavior
		When asked to rate their interest in receiving a parenting skills intervention, all but one parent gave the highest possible rating (very interested)
	Adolescents	Adolescents thought their parents would benefit from skills in the areas of stress management, communication, and conflict reduction
	Staff	Residential staff felt that parents most needed help with monitoring and communication
Timing	Parents	Parents described a mismatch between when it was easiest to attend sessions (while the teen was in residential) and when sessions were typically offered (immediately post-discharge)
		Parents stated a preference for fewer in-person sessions post-discharge
	Staff	Residential staff estimated that at least 2/3 of parents attended sessions while the teen was in treatment, but that fewer than 1/3 attended post-discharge sessions
Computer	Parents	Parents unanimously expressed comfort using computers or smartphones
		Virtually all parents reported looking for information about their teen’s treatment via the internet
		Multiple parents said they wished they could connect with an expert and other parents online
Delivery	Parents	Parents liked the idea of technology as an add-on but didn’t want to lose the “human element”
		Parents rank ordered different delivery options for a parenting intervention: parents most preferred mixed (in-person + computer) support and least preferred computer only
	Staff	Residential staff had a strong preference for a mixed (in-person + computer) approach over computer only

### Study objectives and specific aims

The overarching goal of this protocol is to evaluate the feasibility, acceptability, and preliminary effectiveness of the adapted PW model (PW+) among parents of adolescents (age 12–17) preparing for discharge from acute residential SUD treatment. The project has two phases. In Phase 1, a pilot open trial tests the PW+ protocol with 10 parent-adolescent dyads. Feedback from residential staff, parents, and adolescents will be used to: (a) finalize a manual for adjunct individual coaching sessions, (b) develop coach training materials, and (c) refine the delivery and content of technology-assisted engagement strategies. During Phase 2, a pilot randomized controlled trial with 60 parent-adolescent dyads will evaluate the effectiveness of the PW+ intervention as an adjunct to residential standard care (SC). Combined, the activities in these two study phases will address three Specific Aims.

#### Specific aim 1

To examine the feasibility and acceptability (primary protocol outcomes) of the PW+ technology-assisted intervention among parents of adolescents in residential SUD treatment.

#### Specific aim 2

To examine the preliminary effectiveness of the PW+ technology-assisted protocol on adolescent substance use and associated high-risk behaviors (secondary protocol outcomes) over the first 24 weeks post-discharge.

#### Specific aim 3

To examine the preliminary effects of the PW+ technology-assisted on parental monitoring and communication (putative mediators of the intervention) over the first 24 weeks post-discharge.

## Methods

### Timing of key protocol elements

Table 2 depicts the timing of key protocol elements including enrollment, allocation (in the randomized trial), intervention, and assessments. Two issues related to the timing of protocol components bear mention. First, key procedures (i.e., consent, baseline assessment, randomization, intervention) are conducted immediately after the adolescent’s admission to residential treatment. We start the protocol immediately instead of waiting until after discharge, due to qualitative pilot data (see Table 1) indicating that parents viewed the post-discharge period as overwhelming, and that parents had concerns about their ability to schedule face-to-face sessions during this period. Starting immediately after admission also capitalizes upon a critical intervention window while the teen is in residential treatment. Second, the open trial has one follow-up assessment at 6-weeks post-discharge that focuses on feasibility and acceptability, while the pilot randomized trial has a longer follow-up assessment schedule of 6-, 12-, and 24-weeks post-discharge focused on preliminary effectiveness. Prior studies by members of our team [68, 69], have suggested that brief interventions have their strongest effect between baseline and 24 week follow-up, with significantly less change over subsequent assessments. Having three follow-up assessments during the first 24 weeks post-discharge will serve to elucidate the change that is likely to occur immediately following treatment.

**Table 2 Tab2:** Timing of enrollment, intervention, and assessment activities

Timepoint	Enrollment	Allocation	Residential treatment		Post-discharge period		
	−t1	0	~2 week stay	Discharge	+6 weeks	+12 weeks	+24 weeks
*Enrollment*							
Informed consent/assent	X						
Allocation		X					
*Intervention*							
Standard care			X	X	(Optional)		
PW+ elements							
Coaching (up to 4 sessions)			X	X	X		
Computer program			X	X	X	X	
Text messages					X	X	
Parent online message board					X	X	
*Assessment*							
Primary outcomes: feasibility and acceptability			X	X	X	X	
Secondary outcomes: adolescent outcomes	X				X	X	X
Putative mediators	X				X	X	X

### Residential center

Evaluation of the PW+ intervention will occur at the only acute residential community SUD treatment program in Rhode Island. The facility contains 16 beds and is located about 20 min outside the state capital in a suburban area. It recently affiliated with the local hospital, but continues to operate as an independent community-based program. Average length of stay is 6–10 days. About five adolescents are admitted per week on average, which equates to approximately 260 admissions per year. Based on past year census data, about 30% of adolescents at the residential treatment center are racial/ethnic minorities, with Hispanic (about 20%) and African-American (about 10%) being the most commonly represented minority groups. There is approximately even representation of male and female adolescents. In the pilot qualitative sample, median household income was $30,000, with an extremely wide range from $18,000 to over $200,000.

### Participants

A total of 70 parent-adolescent dyads (10 in Phase 1/open trial and 60 in Phase 2/pilot randomized trial) will be recruited from the acute residential treatment center. To qualify for the study, parents must meet these inclusion criteria: (1) be the parent or legal guardian of an adolescent, aged 12–17 years; (2) had adolescent admitted to residential treatment due to problems related to substance use; (3) will be the primary guardian living with the adolescent immediately post-discharge; (4) willing to receive a parenting intervention; (5) fluent in English or Spanish; and (6) willing to provide written consent and adolescent willing to provide written assent. Adolescents automatically qualify if their parents meet these criteria. The only exclusion criteria are conditions that might preclude the adolescent’s participation in a 2–3 h interview (e.g., mania, psychosis, and cognitive impairment). Based on recent enrollment data, we conservatively expect at least 50% of new admissions to be eligible (with discharge to another facility, discharge to another caregiver, or parent unwilling to receive an intervention as primary reasons for exclusion). To meet our recruitment goal of 70 parent-adolescent dyads, we will need to enroll 25–30% of eligible parents over the first 2 years of the study.

### Study enrollment and randomization

In accordance with institutional review board procedures at Brown University and Rhode Island Hospital, parents of all newly admitted adolescents will receive a Consent to Contact (CoC) form as part of the standard intake process at the residential center. Parents that sign a CoC form will then be contacted by research staff in one of two ways. If the adolescent is admitted Monday through Friday during normal business hours (which accounts for about 80% of new intakes), research staff located on site will immediately approach the parents and invite them to initiate the consent process. If the adolescent is admitted after hours or on weekends, research staff will contact the parents using the preferred contact information provided.

Parents will provide written informed consent and adolescents will provide written assent in separate private rooms at the residential center. If an adolescent chooses not to participate, the parent will be given general feedback that the family did not qualify so as to protect the adolescent’s privacy. Parents and adolescents may choose to conduct the informed consent process and all other study procedures in English or Spanish.

Parents will be given the choice whether to return for the baseline assessment or complete it immediately following informed consent. In the Phase 2 trial, randomization will occur within 24 h after the baseline assessment. Parent-adolescent dyads will be randomized to either SC or PW+ using urn randomization balanced on sex, severity of substance use, and preferred language (English vs. Spanish). Randomization will be conducted by a Co-Investigator, not involved with the assessment process, as soon as a parent consents to participate. Condition assignments will be placed in sealed envelopes and given to the independent evaluator. The evaluator will give parents their sealed envelope indicating that their treatment condition immediately after completion of the baseline assessment. If the parent is assigned to PW+, the evaluator will schedule the first in-person coaching session.

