### Assessments

Parents and adolescents will complete a baseline assessment in-person shortly after their admission to residential treatment. Adolescents will be assured of confidentiality and a National Institute of Health Certificate of Confidentiality (CoC) will be obtained, as adolescent self-report use has shown reliability when confidentiality is assured [77–80]. The CoC will allow the research team to refuse to disclose names or other identifying characteristics of research participants in response to legal demands such as subpoena of records. Follow-up assessments will be conducted by an independent evaluator who is blind to condition. During the open trial, there will be follow-up assessment at 6 weeks post-discharge, while during the pilot randomized trial there will be three follow-up assessments at 6, 12, and 24 weeks post-discharge. Follow-up assessments will be scheduled in-person at the residential treatment center; if a parent no-shows more than twice for a follow-up assessment, then research staff will attempt to conduct the follow-up sessions at a location of the family’s choosing (i.e., home, school). The baseline assessment will be 1.5–2 h and the follow-up assessments will be about 1.5 h (see Table 3 for overview of measures).

**Table 3 Tab3:** Overview of protocol measures

Construct	Measurement/scale	Data obtained
Feasibility	Participation rates	Percent of parents who participate in the study
	Parent engagement	Number of coaching sessions attended, online usage of PW and parent message board (i.e., logins, sessions completed, page views, time spent), number of texts viewed
Acceptability	Withdrawal rates	Percent of parents who withdraw from study
	Exit interviews (open trial only)	Open-ended questions on perceptions of in-person sessions, text messages, computer program, and online message board
	CSQ	Satisfaction with treatment delivery and ability to manage their adolescent’s problems
Adolescent substance use	GAIN days of use	Days of alcohol use, marijuana use, and other drug use
	GAIN SFS	Averages percent of past 90 days during which there was use of alcohol, marijuana, or heavy drugs; intoxication; and failure to perform activities due to use
	Gain SUDS	Assesses substance use disorder symptoms in line with both DSM-IV and DSM-V criteria

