	Biological markers	Saliva alcohol screens (12 h window) and 8 panel urine drug screens testing for marijuana, MDMA, cocaine, amphetamines, methamphetamines, opiates, oxycodone, and benzodiazepines
Adolescent high-risk behavior	GAIN risky sex	Series of items about risky sexual behavior over the past 90 days including number of partner, number of sexual contacts, and number of times had unprotected sex
	GAIN days legal	Days of legal involvement over the past 90 days
	GAIN days school	Days of school attendance/truancy over past 90 days
Parenting	PMQ	Parental monitoring and sources of parental monitoring
	PAC	Assesses positive and negative aspects of general parent-teen communication
	FAsTask video code	In vivo problem solving tasks focused on: limit setting; substance use norms; monitoring and listening

*CSQ* customer satisfaction questionnaire, *GAIN* global appraisal of individual needs, *SFS* substance frequency scale, *SUDS* substance use disorder scale, *PMQ* parental monitoring scale, *PAC* parent-adolescent communication scale

We selected adolescent measures to be as consistent with SC as possible. The residential center typically obtains a urine screen and administers a comprehensive adolescent interview to assess substance use and functioning across multiple life domains. We therefore combine biological markers with the Global Appraisal of Individual Needs—Quick (GAIN-Q3 [81]), a well-validated structured interview that assesses adolescents’ problems across several domains: substance use, school, mental health, physical health, risk behaviors, work, and sources of stress. The GAIN-Q3 substance use scales used in this protocol have demonstrated sound psychometric properties including internal consistency [82], high concurrence with the Timeline Followback Method [83], ability to predict SUD diagnoses made by blind raters (κ = .91) [84], and ability to predict substance-related problems as well or better than biometric markers [82]. The PI is a certified trainer of the GAIN family of instruments with experience analyzing GAIN data [85–88] and will train the independent evaluators.

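### The plan does not separate the evaluator who hands out assignments and books PW+ coaching from the blinded follow-up assessor, and it gives two conflicting times for randomization

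*Protocol article*

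**What the plan says.** All of the allocation text is in the protocol article, Study enrollment and randomization.

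- Holding the assignments: "Condition assignments will be placed in sealed envelopes and given to the independent evaluator".
- Telling the parent: "The evaluator will give parents their sealed envelope indicating that their treatment condition immediately after completion of the baseline assessment".
- Acting on the result: "If the parent is assigned to PW+, the evaluator will schedule the first in-person coaching session".
- Time of the draw, first statement: "In the Phase 2 trial, randomization will occur within 24 h after the baseline assessment".
- Time of the draw, second statement: a Co-Investigator does it, "not involved with the assessment process, as soon as a parent consents to participate".
- Method: "urn randomization balanced on sex, severity of substance use, and preferred language (English vs. Spanish").

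The same section lets parents choose between doing the baseline straight after consent and coming back for it.

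On blinding, the Assessments section says: "Follow-up assessments will be conducted by an independent evaluator who is blind to condition". It later says that the principal investigator "will train the independent evaluators", in the plural.

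**The concern.** Two things do not fit together.

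The first is the role. The title of independent evaluator is given both to the person who handles allocation and to the person who is meant to be blind at 6, 12 and 24 weeks. A sealed envelope can protect the person carrying it, but booking coaching for one arm only cannot. A booking reveals PW+, and the absence of one reveals standard care.

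The second is the order of events. Consent and the end of baseline are different moments and may fall on different days, yet randomization is tied to both. The order decides whether the study's own severity measure can feed the urn, and whether a dyad can enter the intent-to-treat set with no baseline.

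At stake are the adolescent outcome estimates under Aim 2 and, to a lesser degree, the parenting estimates under Aim 3. The Data analysis plan makes effect sizes with 95% confidence intervals the main analytical goal for the secondary outcomes. Sample size and power then uses the observed effect to judge whether a larger trial is warranted and how large it should be. Assessor bias would carry into that decision.

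**Working it through.** No formula applies and the plan gives no figure to reproduce. The check sets the statements side by side.

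**Role**

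1. The evaluator receives the sealed assignment. The arm is still hidden.
2. The evaluator gives it to the parent when the baseline ends. The arm may still be hidden from the evaluator.
3. The evaluator schedules coaching if, and only if, the arm is PW+. The arm is now known for that dyad, whichever arm it is.
4. Follow-up takes place at three later visits and is done by someone with the same role title who is said to be blind.
5. No section says that the person in step 4 differs from the person in step 3. The plural in the training sentence shows that more than one evaluator is expected, but not how the work is divided.

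The extent therefore depends on staffing that the article does not state:

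- Different people for steps 3 and 4: 0 dyads affected.
- One person throughout: all 60 dyads, and up to 60 × 3 = 180 planned follow-up assessments before attrition.
- Several evaluators with no rule: somewhere between, namely the dyads for which the same person did both jobs.

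**Which outcomes are exposed** (Table 3 and Assessments)

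- Most exposed: days of use, substance frequency, disorder symptoms, sexual risk, legal and school days. All come from the GAIN-Q3, an interview.
- Less exposed: saliva and urine screens, and the monitoring and communication scales, which parent and adolescent complete themselves.
- Interaction task: scored from video. The article does not say who codes it.
- Little exposed: the primary outcomes, such as enrollment, session attendance, logins and withdrawal.

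**Timing**

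| Statement | Draw at consent | Draw after baseline |
|---|---|---|
| Randomization within 24 h after baseline | conflicts | fits |
| Randomization as soon as the parent consents | fits | conflicts |
| Envelope handed over directly after baseline | fits | fits only if drawn on the spot |
| Timing section lists baseline before randomization | conflicts | fits |
| Table 2 puts consent and baseline measures in the column before allocation | fits poorly | fits |

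Neither timing satisfies every row, so the text has to be reconciled.

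If the draw is at consent, two consequences follow:

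- The GAIN-Q3 baseline has not yet been taken, so the urn cannot use it for severity. The center's own intake interview and urine screen might supply a severity rating, but the article does not name them as the source.
- A parent who consents and does not come back for baseline is already randomized. The analysis plan includes all 60 parents and adjusts each outcome for its baseline value, which that dyad would lack. The planned comparison of completers with non-completers also uses baseline variables.

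**The case against.** The strongest reply on blinding is that the text can be read consistently. There is more than one evaluator, blinding is claimed for follow-up only, and a condensed article need not describe staffing. One evaluator could do baseline and allocation while another does follow-up. This stands as a possibility. A reader might otherwise infer that blinded follow-up is impossible, or that the assessor knows the arm of all 60 dyads; the article does not establish either. It does use one title for two incompatible tasks and states no separation.

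A reader might also infer that an unblinded assessor would bias every effectiveness estimate. The biological screens and the self-completed scales do not support that, and the GAIN-Q3 is a structured interview, which limits the assessor's latitude without removing it.

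On timing, it could be said that the 24-hour sentence refers to disclosure and the consent sentence to the draw. That would remove the contradiction, but only by settling on a draw at consent, with the consequences shown above. A reader might go further and treat the draw at consent as settled, or the severity balancing as unworkable. Neither follows. The article equally supports a draw after baseline, and severity might come from the center's intake.

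On concealment, the draw is made by someone outside the assessments, after consent, and stays sealed until baseline ends. If the seal holds, failure to return for baseline cannot depend on the arm. Broken concealment is therefore not shown.

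**Conclusion.** The concern holds as two defects in what is written. First, the evaluator who gives out the assignment and books coaching learns the arm of each dyad handled, and nothing keeps that person from doing the follow-up that is described as blind. Second, the time of randomization is stated in two ways that cannot both be true when baseline follows consent and may be on another day.

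The first defect affects between 0 and 60 dyads, depending on unstated staffing, and mainly the GAIN-Q3 outcomes. The document gives no basis for putting a number on the bias. The second matters for severity balancing only if the urn uses the study baseline, and for the ANCOVA only if some dyad is randomized and never assessed; the article gives no expected number of such dyads.

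This should be fixed for the secondary effectiveness and mediator estimates. It does not threaten the primary feasibility and acceptability outcomes.

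**What to change.** 1. State one sequence: consent; baseline completed; then urn randomization by the Co-Investigator, using the recorded baseline severity, within 24 hours. Delete the clause that ties the draw to the moment of consent, and adjust the hand-over sentence, which at present needs the envelope to be ready when baseline ends.
2. Have the Co-Investigator or a coach tell the parent the assignment and schedule coaching, rather than anyone who conducts follow-up assessments. Alternatively, keep the evaluator in that task and state that this person never conducts follow-up for the same dyad.
3. Name the measure of substance use severity that feeds the urn.

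Recording the assessor's guess of arm at follow-up is optional and is not needed to cure either defect.

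The cost is protocol wording and a task moved between existing staff, with no change to sample size or analysis. The parent may learn the assignment up to a day later, which uses part of a stay that averages 6–10 days. The alternative in step 2 needs at least two evaluators, which the plural in Assessments suggests are available. Separation cannot be restored afterwards for a dyad whose follow-up assessor already knows the arm, so it should be in place before the first Phase 2 dyad is randomized.
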